### Sample size calculation

The primary outcomes of the app effectiveness study are the changes in the prevalence of modern contraceptive use, STI testing, STI treatment, and SRH awareness. We propose to estimate the study’s sample size based on the prevalence of modern contraceptive use among the youth aged 18 to 30 years. According to the 2016 Uganda Demographic and Health Survey, the prevalence of modern contraception among the youth aged 18 to 30 years in Uganda is 30.2%. The study utilizes the sample size formula for Z test for two sample proportions used for behavioral studies to compute sample size estimates.

Sample size formula;$$ n=d\left(\frac{{\left({Z}_{1-\alpha /2}\sqrt{2p\left(1-p\right)}+{Z}_{1-\beta}\sqrt{\left({p}_1\left(1-{p}_1\right)+{p}_2\left(1-{p}_2\right)\right)}\right)}^2}{{\left({p}_2-{p}_1\right)}^2}\right) $$

Where:

*n* = sample size.

*d* = design effect.

*p*_1_ = the prevalence of modern contraception.

*p*_2_ = projected prevalence at the end of the study, so that (*p*_2_ − *p*_1_) is the magnitude of change you want to be able to detect.

*p =* (*p*_1_ +*p*_2_)/2.

*Z*_1 − *α*_= the z-score corresponding to desired level of significance.

*Z*_1 − *β*_ = the z-score corresponding to the desired level of power.

The table below shows the required sample size for each group with varying magnitude of change in proportions to be detected, different power sizes, and two-sided level of significance of 0.05.

The study will require a sample size of 435 participants per randomized group in order to obtain 90% power to detect a 15% change in the prevalence of modern contraception at a two-sided of 5% level of significance. The sample size estimations assumed no design effect i.e. d = 1. After adjusting for the 10% non-response rate, a sample size of 479 was computed leading to a total sample size of 958.

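### The planned 435 per group is twice what the protocol's own formula and inputs give, so the stated 90% power for a 15-point change is wrong

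*Protocol article*

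**What the plan says.** The Sample size calculation section of the protocol article sizes the trial on modern contraceptive use and prints a two-proportion Z-test formula. Its inputs are all given there:

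- Baseline: "the prevalence of modern contraception among the youth aged 18 to 30 years in Uganda is 30.2" per cent.
- Effect: p2 − p1, which "is the magnitude of change you want to be able to detect"; the target is "to detect a 15% change in the prevalence of modern contraception".
- Error rates: a "two-sided level of significance of 0.05", with the size chosen "in order to obtain 90% power".
- Design effect: "The sample size estimations assumed no design effect", that is, d = 1.

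The conclusion drawn is: "The study will require a sample size of 435 participants per randomized group in order to obtain 90% power to detect a 15% change". The section goes on: "After adjusting for the 10% non-response rate, a sample size of 479 was computed leading to a total sample size of 958". The Participant recruitment section then draws a random sample of 958 rooms with one participant per room, so the figure carries through to fieldwork.

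**The concern.** The section gives the formula, every input and the answer, so the answer should follow. It does not: 435 is too large by a factor of two for a 15-point difference and far too small for a 15% relative change.

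This is the only numerical justification for the trial's size. If it is wrong, readers and the ethics board are told that 958 students are needed for a target that about half as many would meet. Anyone interpreting a null result would also believe the trial could reliably detect only differences of about 15 points, when it can detect appreciably smaller ones.

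**Working it through.** **Inputs** (all from Sample size calculation): p1 = 0.302; p2 = 0.302 + 0.15 = 0.452; p = (0.302 + 0.452)/2 = 0.377; two-sided α = 0.05 (z = 1.960); power 0.90 (z = 1.2816); d = 1. The change is taken as absolute because the formula defines it as p2 − p1.

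**1. The printed formula**

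n = d × [z(1−α/2) √(2p(1−p)) + z(1−β) √(p1(1−p1) + p2(1−p2))]² / (p2 − p1)²

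- 2p(1−p) = 2 × 0.377 × 0.623 = 0.4697; root 0.6854; × 1.960 = 1.3433
- 0.302 × 0.698 + 0.452 × 0.548 = 0.2108 + 0.2477 = 0.4585; root 0.6771; × 1.2816 = 0.8678
- Sum 2.2111; squared 4.8889; divided by 0.15² = 0.0225 gives **217.3, i.e. 218 per group**

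This is a per-group formula, and the section describes its table as giving the size for each group.

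**2. Reproducing 435**

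2 × 217.28 = 434.57, which rounds up to **435**. So 435 is reproduced as the total for both arms. The same number arises per group with d = 2, but the section states d = 1.

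**3. Other readings of the inputs, per group**

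| Variant | n per group |
|---|---|
| Continuity correction | 231 |
| One-sided 5% (with correction) | 177 (191) |
| Unpooled variance | 215 |
| Arcsine | 218 |
| 95% power (with correction) | 269 (282) |
| 15-point decrease | 162 |
| α divided by 3 or by 4 | 280 or 296 |
| 15% relative change (p2 = 0.302 × 1.15 = 0.347) | 2,244 |

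None gives 435.

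**4. What 435 per group delivers**

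Power = Φ{[Δ√n − 1.960 √(2p(1−p))] / √(p1(1−p1) + p2(1−p2))}

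- For 15 points: (0.15 × √435 − 1.3433)/0.6771 = (3.1285 − 1.3433)/0.6771 = 2.636, so power is **99.6%**.
- For 10 points (30.2% to 40.2%): 87.2%.
- For a 15% relative change (30.2% to 34.7%): about 30%.
- Solving for 90% power: a difference of 0.1049, i.e. **10.5 points** (30.2% to 40.7%).
- With 435 in total (217.5 per group), power for 15 points is 90.0%, the figure the protocol claims.

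**5. Allowance for non-response**

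The plan's 479 is 435 × 1.10 = 478.5, rounded up. To have 435 left after losing 10% requires 435/0.90 = 483.3, i.e. 484. As it stands, 479 × 0.90 = 431.1, so about 431 per arm would be evaluable.

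For the 15-point target: 218/0.90 = 242.2, i.e. 243 per arm and 486 in total. The plan's own multiplication would give 218 × 1.10 = 239.8, i.e. 240 per arm and 480 in total. Against 486, the planned 958 is 1.97 times as large.

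**The case against.** The best defence is that the error is on the safe side. Power for 15 points at 435 per group is 99.6%, and at 431 still 99.5%, so the main comparison is not put at risk and a null result would be more informative than claimed. That is correct, and it limits the harm to a misstated justification and possibly unneeded enrolment.

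The cause is also not certain. Doubling the two-arm total is inferred from the numerical match; a calculation run with d = 2 would give the same 435 per group. The sample-size table is not in the text at hand, so the intended row cannot be checked. This stands as a caution about cause but does not rescue the paragraph: with d = 2 it would contradict its own statement that no design effect was assumed.

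The relative reading of 15% is largely excluded, because the section defines the change as p2 − p1. Wording it as percentage points is therefore a clarification. The 479-versus-484 slip is five people per arm and has no practical effect on power.

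Finally, there may be good reasons not to cut enrolment. The Discussion accepts that students in the two arms will interact. As an illustration on an assumed figure, suppose 20% of a 15-point effect reached controls (0.20 × 15 = 3 points, so 33.2% against 45.2%). Power would then be about 73% with 218 per arm and 95% with 431. This supports keeping 958, but the protocol does not give it as the reason.

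**Conclusion.** The concern holds. On the protocol's own formula and inputs, 90% power for a 15-point change needs 218 per group, not 435. The planned 435 per group has 99.6% power for that change, and its detectable difference at 90% power is about 10.5 points. After a proper allowance for 10% loss, the stated target needs 486 participants against the 958 planned.

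This rests on reading the 15% as percentage points, as the formula requires, and on d = 1 as stated. It is over-sizing and misreporting, not a shortfall in power. How 435 came about is inferred, but the mismatch is not.

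**What to change.** Correct the Sample size calculation paragraph in one of two ways, and check the table against the formula:

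- **Keep 958.** State that 479 randomised per arm, about 431 evaluable after 10% loss, gives 90% power for a difference of about 10.5 percentage points (30.2% to 40.7%) and over 99% for 15 points. This is the safer choice given the contact between arms that the Discussion expects.
- **Keep the 15-point target.** State 218 evaluable and 243 randomised per arm, 486 in total, and change the 958 rooms in Participant recruitment to match. Consider the effect of contact between arms before choosing this.

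If a design effect of 2 was in fact intended, say so, justify it, and remove the statement that d = 1.

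In every case write percentage points rather than a bare per cent, and allow for loss by dividing by 0.90. The cost is rewording one paragraph and checking one table. Keeping 958 needs no extra participants, and the second option reduces enrolment.

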### Participant recruitment

We propose to randomly recruit the study participants from the university halls and private affiliated hostels at KYU. A listing of university halls and affiliated hostels and their estimated population will be prepared with the help of student leaders at the university. Permission to access the halls and hostels will be sought from the respective wardens. We will further conduct a listing of room numbers across the university halls and hostels identified. Rooms will be uniquely identified by the name of hall/ hostel and the room number. A random sample of 958 rooms will be taken and, in every room, only one participant who meets the criteria will be selected. In the event that there is more than one eligible participant in the room, a simple draw lot will be used to select one participant. Several iterations of this sample plan will be made till when the required sample size is achieved. We aim at recruiting 70% females and 30% males on the program. Trained research assistants will move to the selected rooms and recruit the study participants. Recruited participants will first be screened for eligibility before enrollment in the study.

### Randomization and allocation

Enrolled participants will be randomized to two arms of the study in a 1:1 ratio, participants that will receive the App and control participants that will not receive the App. At the time of consent and enrollment, we shall explain to the participants that there is a 50% chance that they receive the app, that the research team will have no control over this, and will not know until the end of the study whether or not they were randomized to receive the app. We will only record the telephone number of the consenting participant, link this to a unique study ID and pass this on to the app developer. The app developer will use a computer generated random sequence of numbers, matched to telephone numbers and study ID to allocate participants to the trial. The app will be available for download from the developer’s repository and will be password protected. To ensure that the treatment is not contaminated, the developer will use a unique one-time password, only useable once by a person (telephone number/ username) that have been randomized to receive the app. Participants randomized to receive the app will receive text messages with the app link and guidelines on how to install the app on their phones. They will further receive more guidelines on how the app will be used and its benefits.

### Blinding/allocation concealment

We shall make every attempt to blind the research team at GHE Consulting to the allocation sequence. Only the app developer will know or have access to this sequence. We propose to use an electronic system of data collection that is managed by the app developer. The statistician at GHE Consulting will have access only to data from the standard questionnaire to track response rates. The app developer will retain all data on app usage and downloads until the end of the study.

### Baseline and follow-up assessments

Enrolled study participants will be followed up at one and six months to determine the effectiveness of *the* SRH App in increasing SRH awareness and uptake*.* A standardized questionnaire has been developed for this study. At enrollment, the research assistant will obtain background information from eligible and consenting participants. We will collect data on the demographic and socioeconomic characteristics, SRH knowledge, sexual behavior and attitude, and SRH uptake (contraception and sexually transmitted infections testing and treatment). Information on SRH uptake will be self-reported at both baseline and end line. Questions on SRH knowledge and sexual behaviors will be modified from the World Health Organization (WHO) SRH guiding questionnaire [40] and the Uganda AIDS Indicator Survey [11]. Questions on SRH uptake will be obtained from the UDHS questionnaire. The questionnaire will be administered to consenting participants at enrollment. At the close of the study (after un-blinding the GHE (U) Ltd. team), we shall conduct an acceptability and user satisfaction survey among participants in the intervention arm of the study. We will also follow up the recruited participants in the two study arms with the standardized questionnaire similar to the baseline questionnaire to assess the impact of the SRH App on program indicators.

### Data collection procedures

We plan to use the smart-phone based Open Data Kit (ODK) app to collect data both at baseline and end line. Research assistants will be trained on the use of smart-phone and ODK for data collection. This will enable the team to collect high-quality data in real time, thereby saving time.

The app developer will also track app download and usage statistics so that at the close of the study we can determine who of those randomized to the study actually downloaded and used the app to access SRH tools and services. We believe this is not only a cost-efficient way to collect the data but will contribute to blind assessments as the GHE Consulting team will not have direct access to mobile contacts. While app use will be managed by the developer, the PI will have access to user statistics through the administrator module of the app.

### Data management

We will separate the responsibility of GHE Consulting and the app developer for data management to ensure the integrity of the research and confidentiality. All data collected at all times will not be identifiable. The app developer will maintain telephone contacts and the random allocation sequence, while the statistician at GHE will maintain app usage statistics. GHE Consulting will maintain records of the standard questionnaire responses and will administer the end-line acceptability and user satisfaction questionnaire. These two data systems will be maintained separately and only linked through unique study IDs.

The app developer will hand over all data to GHE (U) Ltd. at the close of the study. Direct access to analyze, verify and reproduce study data or reports will be granted to the PI, research coordinator, and study statistician. Regulatory entities like Grand Challenges Canada (GCC) and the MUST IRB that may want to monitor the study will be granted access to study procedures and data where requested. Pursuant to our contract with Grand Challenges Canada, the original source documents, study records, and reports will be stored intact for a period of ten years after the study ends.

### Study outcomes

The primary outcome of the study is the magnitude of change in the SRH services uptake measured by the proportion change of modern contraceptives use and testing and treatment for sexually transmitted infections at month six. The secondary outcomes are changes in participant’s knowledge of SRH and sexual behaviors at month six.

### Primary analysis

We will assess the differences at baseline between the intervention and control arms. Observed group differences for each variable will be summarized using means and proportions. The primary analysis will be an intention to treat analysis (ITA). The magnitude of change in proportion between the two groups provides a potentially unbiased estimate of the average treatment effect (ATE) of the SRH App. We will use a two-sample proportion Z-test to test the null hypothesis that the two sample changes in proportions are significantly different at month six at 5% level of significance. We will also carry out a difference in difference (DID) analysis to identify the magnitude of change as a result of the SRH App. We will also compare the changes in the different contraceptive methods and STI tests self-reported at six months by study arm.

We will conduct binary regression analysis with the primary outcome as the response variable and the participant characteristics as the explanatory variables. We shall adjust for any confounding influence that may arise from the participant belonging in any study arm or time point of data collection by adding the study arm and time point as explanatory variables in the regression model.

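### The primary test is stated as a two-proportion Z-test on changes, with the null worded backwards; if it is run that way its standard error is wrong

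*Protocol article*

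**What the plan says.** Under Primary analysis, the article commits to intention to treat and then states: "We will use a two-sample proportion Z-test to test the null hypothesis that the two sample changes in proportions are significantly different". The comparison is placed at month six and uses a 5% significance level. The section continues: "We will also carry out a difference in difference (DID) analysis to identify the magnitude of change as a result of the SRH App". A binary regression follows, which handles arm and time by "adding the study arm and time point as explanatory variables in the regression model". No arm-by-time term is named, and the baseline value of the outcome is not named as a covariate.

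The language of change is used elsewhere too. Study outcomes says: "The primary outcome of the study is the magnitude of change in the SRH services uptake measured by the proportion change of modern contraceptives use". The same sentence goes on to include STI testing and treatment, measured at month six. Sample size calculation says: "The primary outcomes of the app effectiveness study are the changes in the prevalence of modern contraceptive use, STI testing, STI treatment, and SRH awareness". Under Baseline and follow-up assessments, the same participants self-report uptake at baseline and at end line.

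The sample size rests on a different quantity: "The study utilizes the sample size formula for Z test for two sample proportions". That formula compares two independent proportions and has no term for a repeated measurement.

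**The concern.** A person's change in a yes/no outcome is −1, 0 or +1. The net change in an arm can be zero or negative, and its variance depends on how strongly each person's two answers are correlated. The two-proportion Z-test takes its variance from p(1−p)/n, which describes neither feature. Applied to changes, it therefore produces a standard error that belongs to another quantity.

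The trial's main p-value is at stake. The stated sentence can be carried out in at least three ways (Z-test on net changes, four proportions treated as independent, month-six proportions only), and these have very different error rates on the same data. The text also does not say outright whether the Z-test, the difference-in-differences (DID) or the regression decides.

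The null as printed is that the changes differ, whereas the null to be tested is that the arms do not differ. That is a slip in wording. It has no numerical effect and is not the cause of the standard error problem.

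**Working it through.** **Inputs from the protocol article:** baseline prevalence p₀ = 0.302; planned change 15%, read as 15 points (p₂ = 0.452); 90% power; two-sided 5%; design effect 1; n = 435 per arm.

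**Assumed, because the article does not give them:** within-person correlation ρ = 0.3, 0.5, 0.7; a common rise c in both arms of 5, 10 or 15 points under no effect.

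**The plan's own figure.** The printed formula with p₁ = 0.302 and p₂ = 0.452 gives 217.3, so 218 per arm. It does not give 435 per arm; 2 × 217.28 = 434.6, so 435 matches the total of both arms. That is a separate point. It does not affect the error rates below, because n cancels in the ratio of standard errors.

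**Step 1, variances.** With v = p(1−p):
- Z-test applied to net changes: SE = √[2c(1−c)/n].
- Correct paired variance of a change, per arm: s = v₀ + v₆ − 2ρ√(v₀v₆), and SE = √(2s/n).
- Four proportions treated as independent: SE = √[2(v₀ + v₆)/n].

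**Step 2, one case in full** (c = 0.05, ρ = 0.3). v₀ = 0.302 × 0.698 = 0.2108; v₆ = 0.352 × 0.648 = 0.2281; s = 0.4389 − 0.6 × 0.2193 = 0.3073.
- Net-change Z-test SE: √(2 × 0.05 × 0.95/435) = 0.0148.
- Correct SE: √(2 × 0.3073/435) = 0.0376.
- Independent SE: √(2 × 0.4389/435) = 0.0449.
- False-positive rate, net-change Z-test: 2[1 − Φ(1.96 × 0.0148/0.0376)] = 0.44.
- False-positive rate, independent: 2[1 − Φ(1.96 × 0.0449/0.0376)] = 0.019.

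**Step 3, false-positive rate of the Z-test on net changes** (analytic):

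| Rise in both arms | ρ = 0.3 | ρ = 0.5 | ρ = 0.7 |
|---|---|---|---|
| 5 points | 0.44 | 0.36 | 0.24 |
| 10 points | 0.30 | 0.22 | 0.11 |
| 15 points | 0.22 | 0.14 | 0.06 |

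Simulation of paired binary data agrees: 0.455, 0.374 and 0.247 at 5 points; 0.300, 0.220 and 0.114 at 10 points. If neither arm changes on average, the test cannot be computed in about 51% of simulated trials. Treating the four proportions as independent gives 1.9%, 0.6% and 0.04% at ρ = 0.3, 0.5 and 0.7. A plain month-six Z-test and a DID with paired variance both hold about 5% (0.048 to 0.051 in the 5- and 10-point simulations).

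**Step 4, precision** (435 per arm, control unchanged at 0.302, treated rising to 0.452; baseline-adjusted variance approximated as (1−ρ²)v₆ per arm):

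| ρ | DID variance ÷ adjusted variance | Power, DID | Power, month six only |
|---|---|---|---|
| 0.3 | 1.48 | 97.9% | 99.6% |
| 0.5 | 1.28 | 99.7% | 99.6% |
| 0.7 | 1.13 | >99.9% | 99.6% |

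Even at ρ = 0 the paired DID has 91.5% power for 15 points.

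**The case against.** The strongest reply is that the authors meant a plain comparison of month-six proportions. The Primary analysis section describes the treatment effect as a change between the two groups, places the test at month six, and then adds a DID, which would be largely redundant if the Z-test already compared changes from baseline. The sample size formula fits that reading, and under it the standard error is correct. The article also prints no standard error for the test, and variance details are commonly left to an analysis plan that is not shown.

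Much of this stands. The wrong standard error is conditional on the test being run on changes as written. But Primary analysis, Study outcomes and Sample size calculation all speak of changes, so the text has to be corrected on either reading. An analysis plan can add detail to a named test; it cannot make that test suit a quantity it does not fit.

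Three stronger readings are tempting and are not supported:
- *That the false-positive rate is bound to be far above 5%.* It depends on an assumed common rise and an assumed correlation. It falls to 6% at 15 points and ρ = 0.7, and to about 2% at 15 points and ρ = 0.8.
- *That using change scores leaves the trial underpowered.* At a 10-point effect and ρ = 0.3 the DID has 76% power against 87% for month six alone, but the plan's 15%, read as points, leaves a correct DID above 90%. From ρ of about 0.5 upwards the DID matches or beats month six alone.
- *That no analysis has precedence.* The Z-test comes first and is the only one tied to a null hypothesis, and the DID is introduced as an addition. The order is implied, though it should be explicit.

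**Conclusion.** The point holds as a defect in what the article states: the named primary test does not fit the named quantity, and the null is worded the wrong way round. If the Z-test is run on changes, the false-positive rate is roughly 6% to 45% over common rises of 5 to 15 points and correlations of 0.3 to 0.7. If the four proportions are treated as independent, it is roughly 0% to 2%. If month-six proportions are compared, it is 5% and only the wording is wrong, with the baseline answer unused. The correlation and the common rise are assumptions; the baseline prevalence and 435 per arm are the plan's own.

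The loss of precision from a DID (variance about 1.1 to 1.5 times that of a baseline-adjusted analysis) is a secondary matter, not a reason to doubt the stated power. The case for acting is that the main p-value should have one valid definition before allocation is unblinded.

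**What to change.** 1. State the null as no difference between randomised arms in month-six uptake.
2. For each primary uptake outcome listed under Study outcomes (modern contraceptive use, and STI testing and treatment), make the primary analysis a month-six comparison of arms adjusted for the participant's own baseline value of that outcome. Report it as a risk difference with a 95% CI. Adjusting for sex as well is optional.
3. Name the DID as a sensitivity analysis, with participant-level (paired) standard errors.
4. State that the regression with arm and time point is supportive. If it is meant to estimate the app's effect, give it an arm-by-time term and account for repeated answers from the same person.

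This keeps the primary outcomes as Study outcomes lists them. The cost is a change of analysis wording: uptake is already collected at baseline, and no extra participants, visits or questions are needed.

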## Plain English summary

We purpose to develop a mobile phone application (app) to increase awareness and uptake of sexual and reproductive health (SRH) services among youth aged 18 to 30 years in Uganda. This app is intended to link users to health facilities where they can access SRH goods and services. It will also reduce on the challenge of poor access to SRH services due to lack of privacy and confidentiality: the app allows users to make orders online and goods are delivered to pick up points of individuals’ choice. We will partner with an app developer to develop the app. We will then pilot this study among students of Kyambogo university, and participants who will download the app will be followed up at 1, 3 and 6 months. We will collect data on app usage from the server, and perform analyses to determine technical performance, impact (increase in SRH demand and usage), acceptability, usability, and cost effectiveness. The prototype app includes an advertising interface to enable corporations and other business entities to collaborate as potential advertisers and to generate revenue for sustainability. If successful, we propose to extend the program to all the youth in the country who own a smart phone but, also, include other services.

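### The binary regression with time point as a covariate takes a baseline and an end-line record from each student but makes no allowance for their correlation, so its standard errors are wrong

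*Protocol article*

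**What the plan says.** The Primary analysis section of the protocol article plans a "binary regression analysis with the primary outcome as the response variable and the participant characteristics as the explanatory variables". It then says that any influence of arm or visit will be handled by "adding the study arm and time point as explanatory variables in the regression model". It names no participant-level term, paired method or variance estimator, and no other section does so either.

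The records come from the same people. Under Baseline and follow-up assessments, the team will "follow up the recruited participants in the two study arms with the standardized questionnaire similar to the baseline questionnaire", and the same section states that uptake is self-reported at the baseline and end-line assessments. Data collection procedures likewise plans to use the electronic forms "to collect data both at baseline and end line". Study outcomes places the primary outcome at month six.

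The visit schedule is broader than these two occasions. Baseline and follow-up assessments says "Enrolled study participants will be followed up at one and six months", and the Plain English summary says "participants who will download the app will be followed up at 1, 3 and 6 months". Neither sentence says that uptake is recorded at the intermediate visits.

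The Primary analysis section also lists a two-sample Z-test at month six and a difference-in-difference (DID) analysis. It does not say how the DID will be fitted.

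**The concern.** A covariate for time point cannot vary unless the data are stacked, with one row per student per visit. Adding it shifts the predicted level between visits. It does not tell the model that two rows belong to the same student. An ordinary binary regression then counts two correlated answers as two independent people.

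The error runs in opposite directions for different terms. Comparisons between students (arm, sex, age, year of study) look more precise than they are. Comparisons within students (change over time, and a DID if it is fitted in the same model) look less precise than they are. The first gives falsely significant predictors and a falsely significant arm term. The second discards the gain from measuring each student twice.

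This is separate from the question of which effect the arm coefficient estimates when no arm-by-time term is present. It concerns the uncertainty attached to the coefficients.

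**Working it through.** **Inputs.**
- From the article: two uptake records per student (Baseline and follow-up assessments; Data collection procedures); 1:1 allocation; two-sided 5% level; baseline prevalence 30.2% and 435 per group (Sample size calculation); 70% female (Participant recruitment).
- Not in the article: the within-student correlation r. I assume 0.3 to 0.5 and show 0.7 as an upper case. The directions below hold for any positive r.
- The article gives no standard error to reproduce. The 435 is taken as stated and only sets the size of the simulation; the standard-error ratios in the formulas do not depend on it.

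**Formulas (linear approximation, two records with common variance s²).**
- Between-student terms use the student mean. Its true variance is s²(1 + r)/2, against s²/2 under independence. True/reported SE = √(1 + r).
- Within-student terms use the student's change. Its true variance is 2s²(1 − r), against 2s² under independence. True/reported SE = √(1 − r).
- Actual rejection rate of a nominal 5% test = 2 × [1 − Φ(1.96 / ratio)].

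| r (assumed) | Arm, fixed characteristics: true/reported SE | Actual error | Time or DID: true/reported SE |
|---|---|---|---|
| 0.3 | √1.3 = 1.14 | 8.6% | √0.7 = 0.84 |
| 0.5 | √1.5 = 1.22 | 11.0% | √0.5 = 0.71 |
| 0.7 | √1.7 = 1.30 | 13.3% | √0.3 = 0.55 |

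**Simulation of the model as written.** Logistic regression on arm, sex and time; 435 per arm; prevalence 30.2%; no true effects; two records per student; 1,500 runs. The correlation between the two binary answers was about 0.28 or 0.48.

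| Term | Reported/true SE (r ≈ 0.28; 0.48) | Rejection, ordinary SE | Rejection, SE clustered on student |
|---|---|---|---|
| Arm | 0.90; 0.81 | 8.0%; 11.4% | 4.7%; 5.1% |
| Sex | 0.87; 0.82 | 9.7%; 10.3% | 5.9%; 4.8% |
| Time | 1.19; 1.40 | 2.1%; 0.5% | 5.1%; 4.7% |

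Simulation error on a 5% rate is √(0.05 × 0.95 / 1,500) = 0.6 percentage points, so the clustered results are consistent with 5%.

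**With an arm-by-time term added (r ≈ 0.48).** The arm coefficient becomes the baseline contrast, which rests on one record per student. Its reported/true SE is 0.98, which is about right. The arm-by-time coefficient, which is the DID, has reported/true SE 1.36 and rejects 0.7% of the time under the null. Clustering restores this to 5.4%. The sex term is still understated (0.84). The simulated DID ratio inverts to 1/1.36 = 0.73, close to √(1 − 0.48) = 0.72 from the formula.

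**The case against.** The strongest reply is that the article says only that a binary regression will be used. It names no variance estimator and assumes no independence, and the same regression with clustered standard errors would fit every word of it. A choice of that kind is often left to an analysis plan, which is not shown here. A fuller plan may well contain it. But the article is not silent on repeated visits: it says how they will be handled, by a covariate, and that handling does not deal with the correlation. Followed as written, it gives wrong intervals.

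Three further objections stand, and each limits the point.

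- **Three records.** A reader might infer from the one-month and six-month follow-up that each student gives three uptake records. The same approximation would then give error rates of 12% to 21% for r from 0.3 to 0.7. The documents do not support this. Uptake is stated to be collected at baseline and end line, and a third record would need uptake to be collected at month one as well.
- **Every coefficient, whatever the model.** A reader might infer that the arm term stays too precise after an interaction is added. It does not. The inflation for arm belongs to the main-effects model only.
- **The main test of effect.** A reader might infer that the headline comparison of arms is made too liberal. The stated significance test is the month-six Z-test, a separate analysis that this point does not touch. The DID would err on the cautious side, and only if it is fitted in the stacked model, which the article does not say. A DID computed from each student's own change would not have the problem.

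**Conclusion.** The point holds for the stacked regression as written. With two records per student and an assumed within-student correlation of 0.3 to 0.5, the true standard errors for arm and fixed characteristics are about 1.14 to 1.22 times those reported. Nominal 5% tests run at about 8% to 11%, rising to 13% at a correlation of 0.7. The standard error for time is too large.

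If an arm-by-time term is added, or the DID is fitted in the same model, the arm term is about right. The true DID standard error is then only 0.84 to 0.71 of the reported one, so DID intervals are 1.19 to 1.41 times as wide as they need to be (1/0.84 and 1/0.71).

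Two things are assumed: that the ordinary model-based standard errors would be used, since no other kind is named, and the size of the correlation, which the article does not give. The direction of each error needs only that the correlation is positive. That is plausible when the same student reports the same behaviours twice within six months.

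**What to change.** In the Primary analysis section, state that the stacked regression will be fitted by GEE with an exchangeable working correlation, or as the same binary regression with standard errors clustered on study ID. State that the DID, if obtained from that model, will be fitted the same way, and that all intervals and p-values will come from that fit.

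An alternative is to model the month-six outcome once per student, with the baseline value as a covariate. That removes the repeated records altogether.

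The cost is one clause of text and one software option. No new data are needed, because Data management already links the data systems by unique study ID. With several hundred students per arm, clustered standard errors are reliable, as the simulation shows. If uptake will also be recorded at month one, the section should say so; the same clustering then covers the third record.
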